**Figure 1 Fig2:**
[figure not shown]
BALANCE pilot RCT intervention flow diagram.

### Blood samples for procalcitonin

Blood samples will be drawn on the randomization day and at days 7, 10 and 14 from the index blood culture collection to measure procalcitonin (PCT) levels. The PCT levels will be batched and measured at the end of the study for the sub-study assessing the association between PCT and clinical outcomes among patients receiving 7 versus 14 days of treatment. The results will not be made available to the treating team, because this could unduly influence clinical practice and protocol adherence, and is ethical because none of the participating sites are currently using PCT as part of routine clinical practice. Following study completion, we will compare PCT area-under-the-curve (AUC) and day 14 PCT levels among patients receiving 7 versus 14 days of antibiotics. We will also confirm whether 7 days of antibiotics is non-inferior to 14 days of antibiotics for bacteremia, in subgroups with both normal and abnormal PCT levels on day 7.

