### Ethics and informed consent

The study protocol has been approved by the Sunnybrook Health Sciences Research Ethics Board and the Queen’s University Health Sciences and Affiliated Teaching Hospitals Research Ethics Board (for Kingston General Hospital), and will be sought at other participating sites. After seeking permission from the treating team, the research coordinator/site primary investigator will approach eligible patients (or their substitute decision-makers) as soon as their blood cultures are positive to obtain informed consent (see Additional file 2). Consent can be delayed at maximum to the 7th day of adequate antibiotic treatment. Critically ill patients are frequently unable to provide initial consent due to altered level of consciousness or understanding. Hence, the Canadian Critical Care Trials Group (CCCTG) has standard operating procedures to seek assistance from substitute-decision makers on behalf of patients. This process has been found feasible and acceptable to patients, decision-makers, and research ethics boards across Canada and has been successfully employed among dozens of CCCTG RCTs [32-35]. We will use this enhanced approach to consent, employing 13 previously described strategies distributed over three phases: preparation for the consent encounter, the consent encounter, and as follow-up to the consent encounter [34].

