### Trial interventions

We will randomize patients to receive a shorter duration of adequate antimicrobial therapy (7 days) versus a longer duration (14 days). Adequate antimicrobial treatment will be defined as a regimen with *in vitro* activity against the organism(s) responsible for the bloodstream infection; the duration of adequate treatment will be determined as the cumulative number of calendar days for which adequate treatment is delivered beyond the date of collection of the index blood culture specimen- the clock will start from initiation of the first adequate treatment dose after the blood culture has been drawn. The selection of specific antimicrobial agents, doses and route of delivery will initially be at the discretion of the treating clinical team. Most commonly the patient will already be receiving some empiric antibiotic treatment for suspected infection prior to the blood culture being documented as positive; the study protocol will not expose patients to potential antibiotic treatment delays. As soon as blood culture results are available (preliminary Gram staining), the research coordinator, in consultation with the site investigator and site infectious diseases co-investigator if necessary, will review the initial antibiotic choice to ensure adequate empiric coverage for the potential culprit organism(s). As blood culture results are finalized (speciation and sensitivity determination), they will re-review the antibiotic choice to ensure that the spectrum of activity is adequate. If the spectrum is inadequate, this will be communicated to the treating physicians. To avoid differentially influencing antibiotic choices and clinical decision-making, the randomization assignment will not be communicated to the study research coordinator, study critical care or infectious diseases investigators or clinicians until the end of day 7. The ICU research coordinator at each site will visit daily to ensure protocol adherence (antibiotics are stopped at the pre-specified date (end of the 7th or 14th day) and not earlier (Figure 1).

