**Figure 2 Fig1:**
[figure not shown]
Determination of day 7 of antibiotic treatment. Multiple scenarios are provided to determine how day 7 of antibiotic treatment will be determined based on days of receipt of adequate antibiotic treatment after collection of the positive blood culture. Adequacy of treatment will only be measurable after the culture and susceptibility result has been finalized.

Calculating day 7 of adequate antibiotics is a complex procedure; there are multiple potential scenarios of adequate and inadequate antibiotic treatment days prior to the culture results being finalized. Figure 2 demonstrates some of the possible scenarios, to illustrate calculation of day 7 from the positive blood culture collection date. The day 7 unblinding date will be calculated as the cumulative number of calendar days the patient receives adequate antibiotics after the positive blood culture collection date. Adequacy of antibiotics will only be definable after the final susceptibility report is available. If a patient received inadequate antibiotics after the positive blood culture collection and before the culture is finalized (Figure 2, scenario 3), day 7 date will be calculated from the date adequate antibiotics were started, which should be immediately after the culture is finalized. If a patient received adequate antibiotics for one day after positive blood culture collection and then was switched to inadequate antibiotics until the culture was finalized (Figure 2, scenario 7), then this one day of adequate antibiotic after positive culture collection will still be counted in the calculation of the day 7 date. Once the culture is finalized, adequate antibiotic treatment should be started/continued without any break until the completion of the assigned treatment duration based on study arm. Discontinuation or missed treatment before the completion of the assigned treatment duration will be considered to be a protocol violation.

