### Analysis of secondary outcomes

Mortality rates (at ICU discharge, hospital discharge and 90 days) will be measured as the proportion of patients alive or dead at these time points. We hypothesize that mortality rates will be non-inferior with 7 days of treatment; the main BALANCE trial will be powered to test this hypothesis. Continuous secondary outcomes, including lengths of stay in ICU and hospital, and durations of ventilation and vasopressor use, will be compared by Wilcoxon test. We will compare the ‘difference in differences’ between day 7 to 14 procalcitonin levels in the two treatment groups.

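### Procalcitonin sampling is timed from the index blood culture, but the arms separate on the adequate-treatment clock, so delayed adequate treatment dilutes the between-arm procalcitonin comparisons

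*Protocol article*

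**What the plan says.** **Sampling clock.** The section Blood samples for procalcitonin states: "Blood samples will be drawn on the randomization day and at days 7, 10 and 14 from the index blood culture collection". The Methods/Design part of the Abstract uses the same clock.

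**Treatment clock.** Under Trial interventions, "the clock will start from initiation of the first adequate treatment dose after the blood culture has been drawn". The text with Figure 2 says: "The day 7 unblinding date will be calculated as the cumulative number of calendar days the patient receives adequate antibiotics". Under Randomization and allocation concealment, the coordinator enters the day-7 date and the assignment is released on it. Until then neither the coordinator nor the clinicians know the arm.

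**Delay is foreseen.** For a patient whose antibiotics were inadequate until the culture was finalized (scenario 3), "day 7 date will be calculated from the date adequate antibiotics were started, which should be immediately after the culture is finalized". Scenario 7 covers one adequate day followed by inadequate days.

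**Consent.** Under Ethics and informed consent: "Consent can be delayed at maximum to the 7th day of adequate antibiotic treatment". Randomization follows as soon as consent is given.

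**Analyses.** Under Blood samples for procalcitonin, "we will compare PCT area-under-the-curve (AUC) and day 14 PCT levels among patients receiving 7 versus 14 days of antibiotics", together with a non-inferiority question in subgroups defined by a normal or abnormal day-7 level. Under Analysis of secondary outcomes: "We will compare the ‘difference in differences’ between day 7 to 14 procalcitonin levels in the two treatment groups".

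**The concern.** The two clocks agree only in patients whose treatment was adequate from the start. The article adjusts the treatment date for everyone else but leaves the procalcitonin dates on the culture clock. Nothing in the text shown re-times the samples.

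The procalcitonin analyses compare the arms. Such a comparison is informative only over the time in which the arms are treated differently, which starts at the end of adequate day 7. If part of the culture-day 7 to 14 interval is spent on identical treatment, the day-14 level, the area under the curve and the day 7 to 14 change all carry less of the contrast.

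The subgroup has a related problem. The useful value is the level when one arm stops and the other continues. In a delayed patient the culture-day-7 value is taken earlier in the course, so an abnormal result may partly reflect late adequate treatment rather than the response to seven days of it.

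**Working it through.** The plan gives no figure on this point to reproduce. The check is calendar arithmetic.

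**Inputs**
- Sample days s = 7, 10 and 14 from culture (Blood samples for procalcitonin).
- The arms separate at adequate day 7, and the longer course ends at adequate day 14 (Trial interventions; text with Figure 2).
- Latest consent is adequate day 7 (Ethics and informed consent).
- d = number of inadequate days after culture and before the day-7 date. The documents give no distribution for d, so 0 to 7 is shown as a range.
- Numbering convention: with d = 0, culture day and adequate day coincide.

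**Formulas**
- Culture day of separation = 7 + d.
- Days from separation to a sample = s − (7 + d). A negative value means the sample precedes separation.
- Share of the culture-day 7 to 14 window in which the arms differ = (7 − d)/7.
- End of the longer course = culture day 14 + d.

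**Results**

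| d | Separation, culture day | Day-7 sample | Day-10 sample | Day-14 sample | Share of window | Longer course ends |
|---|---|---|---|---|---|---|
| 0 | 7 | 0 | 3 | 7 | 100% | 14 |
| 1 | 8 | −1 | 2 | 6 | 86% | 15 |
| 2 | 9 | −2 | 1 | 5 | 71% | 16 |
| 3 | 10 | −3 | 0 | 4 | 57% | 17 |
| 4 | 11 | −4 | −1 | 3 | 43% | 18 |
| 5 | 12 | −5 | −2 | 2 | 29% | 19 |
| 6 | 13 | −6 | −3 | 1 | 14% | 20 |
| 7 | 14 | −7 | −4 | 0 | 0% | 21 |

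Worked case, d = 3: separation is on culture day 7 + 3 = 10. The day-7 sample falls on adequate day 7 − 3 = 4, the day-10 sample falls at separation, and the day-14 sample falls 14 − 10 = 4 days after it, on day 11 of the longer course. The share is (7 − 3)/7 = 57%. For every d of 1 or more, the day-14 sample precedes the end of the longer course.

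**Late consent.** The latest consent is on culture day 7 + d.
- d = 0: the latest consent is culture day 7. The randomization and day-7 samples coincide, and the later samples remain 3 and 7 days after separation. No contrast is lost.
- d of 1 or more: consent can fall after culture day 7, so the day-7 sample may not exist.
- d of 4 or more: 7 + d exceeds 10, so the day-10 sample can be missing too.

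**After the fix.** On the treatment clock the samples fall 0, 3 and 7 days after separation for every d, and the latest permitted consent cannot fall after the day-7 sample date.

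**The case against.** The culture date is a defensible time zero for part of the sub-study, which also looks at how procalcitonin relates to outcome and whether it adds prognostic value. The Abstract and the procalcitonin section agree on that clock, so those two places do not contradict each other. Coverage is reviewed at the Gram stain and again when the culture is finalized, which should shorten d. The article does not define the window for the area under the curve, and that detail can fairly be left to a fuller document. All this stands, but it does not help the comparisons between arms, which need the treatment clock. Analysing by treatment day would help in part, but it cannot recover a sample that was not drawn at separation.

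A reader might infer more than the documents support:
- **That the samples miss the contrast altogether.** The day-14 sample falls after separation for any d below 7, so the contrast is attenuated.
- **That late consent alone does harm.** It matters only together with delay, and then through missing reference values. Consent after adequate day 7 is not allowed.
- **That the arms are compared with bias.** Delay arises before separation and the assignment is concealed until day 7, so delay and the resulting missing samples should be balanced in expectation.
- **That an average loss can be quoted.** If 20% to 40% of patients had delays of 2 to 4 days, the average lost window would run from 0.2 × 2/7 = 6% to 0.4 × 4/7 = 23%. Those inputs are assumptions. The result measures calendar time, and equals lost procalcitonin effect only if the separation accrues linearly, which nothing in the article supports.

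**Conclusion.** The point holds as a mismatch of clocks that weakens the between-arm procalcitonin comparisons in patients with delayed adequate treatment. Per patient, the share of the day 7 to 14 window that carries the contrast is (7 − d)/7. The day-7 subgroup value is taken d days before the arms separate, and delay combined with late consent can leave that value missing.

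The consequence is dilution and missing data in a secondary sub-study. The pilot's primary outcomes, recruitment and adherence, are untouched. The per-patient arithmetic rests only on the article's own rules. The overall effect depends on the distributions of d and of consent time, neither of which is given. It is worth correcting now because it is cheap and because, under Trial status, pilot patients may be carried into the main trial.

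**What to change.** In the Abstract and in Blood samples for procalcitonin, time the three later samples on the adequate-treatment clock: on the day-7 date already entered for release of the assignment, then 3 and 7 days after it in both arms. (Stating the last two as offsets avoids ambiguity in the shorter arm, where no further treatment days accrue.) Define the day-7 subgroup and the day 7 to 14 comparisons on the same clock.

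Keep the randomization-day sample and the early trajectory, since decline in procalcitonin is a listed secondary outcome. Record each sample's day from culture as well, so that prognostic analyses can still use that origin.

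Cost: a change of wording and of the sampling schedule, with the same number of samples. In delayed patients the later samples are drawn d days later, when somewhat more patients may have left. The article's retrospective data put 27% out of the ICU on or before adequate day 7 and 4% out of hospital before it, so some samples will need to be drawn on the wards and a few may be lost.

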### Randomization and allocation concealment

Randomization will occur as soon as the consent is obtained. The web-based randomization system for BALANCE will be created using RANDOMIZE.NET (http://www.randomize.net/), and will employ variable block sizes, stratified by ICU site. After the full susceptibility results become available, the site research coordinator along with site co-investigators will determine the date for day 7 unblinding, taking into account the number of days that the patient has already received adequate antibiotics after the blood culture collection date. At day 7 (date entered by the research coordinator), another email will be sent with the unblinded treatment assignment for the patient. At this time the unblinded treatment for that patient will be displayed in the reports available to the site research coordinator. If a patient is randomized to the shorter (7 day) treatment arm, the treating team will be informed to stop the antibiotics at the completion of 7 days of antibiotics appropriate for the causative pathogen; if the patient is randomized to the longer (14 day) arm the team will be instructed to continue the antibiotic until that date.

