### Statistical analysis

#### Sample size

To estimate our expected adherence rate of 90% within a margin of error of ± 5% (that is, actual adherence 85 to 95%), with 95% confidence, we plan to enroll 115 patients. At our expected recruitment rate of 1 patient/site month across 15 sites, we will need approximately 10 to 24 months to recruit these 115 patients given variability in site trial start-up steps (REB approval, data sharing agreements and contracts). By the time we have recruited 115 patients, we will know with 95% confidence that this number of sites would be able to recruit 95 to 138 patients over the same time interval in a future trial; this data will then be used to estimate the number of centers needed for the main trial (see Additional file 1 for detailed sample size calculation).

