### Data Safety and Monitoring Committee (DSMC)

After broad discussion and engagement of the CCCTG it was determined that a DSMC would not be required for this pilot study, given the short duration of enrolment, and that it is underpowered to examine mortality. A DSMC will be instituted for the subsequent main BALANCE trial [51]. DSMC composition will follow accepted norms of content expertise (critical care, infectious diseases, methodology, and biostatistics) and independence from the investigators and steering committee.

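### The pilot's procalcitonin sub-study promises a non-inferiority answer in two day-7 subgroups, which 115 patients cannot give and which, if the outcome is mortality, does not fit the rest of the protocol

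*Protocol article*

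**What the plan says.** The section Blood samples for procalcitonin describes batched assays at the end of the study and a comparison of PCT between arms after completion. It then adds: "We will also confirm whether 7 days of antibiotics is non-inferior to 14 days of antibiotics for bacteremia". The answer is sought separately for patients whose day-7 PCT is normal and for those in whom it is not. No outcome is attached to that comparison.

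Other sections bear on it:

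- Background gives non-inferior survival as the primary aim of the main trial.
- Analysis of secondary outcomes hypothesises non-inferior mortality with 7 days and says that "the main BALANCE trial will be powered to test this hypothesis".
- Subgroup analyses lists four analyses for the pilot and calls them exploratory. PCT is not among them.
- Data Safety and Monitoring Committee (DSMC) justifies having no committee partly because "it is underpowered to examine mortality".
- Sample size bases the 115 patients on the precision of the adherence proportion, not on any comparison of arms.
- Frequency of analyses places the analyses at the end of the pilot. Trial status says that pilot patients will be rolled into the main trial if no substantive protocol change is needed.

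**The concern.** A statement that a study will confirm whether one treatment is non-inferior to another commits it to a verdict. Here the verdict is promised twice, once per PCT subgroup, in a feasibility trial that elsewhere leaves the mortality hypothesis to its successor. If the whole pilot cannot examine mortality, parts of it cannot either.

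Taken literally, the sentence leads to one of two poor outcomes. The likelier is that non-inferiority is not shown even though the arms are equal, because the interval is too wide. The other is that a wide, non-significant difference is read as support for 7 days in one PCT group. Pilot patients may later count in the main trial, so such a reading would concern the main trial's own question.

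**Working it through.** **The plan's own figures.** The article gives no sample size or power for the PCT comparison. Its 115 is tied to estimating 90% adherence within 5 points with 95% confidence. The usual normal-approximation formula gives 1.96² × 0.90 × 0.10 / 0.05² = 138.3, so 139 patients; with 115 the half-width is 1.96 × √(0.09/115) = 5.5 points. The simple formula therefore does not return 115, but the detailed calculation is in Additional file 1, which is not shown. The accompanying recruitment range of 95 to 138 does reproduce, as the exact Poisson 95% interval for a count of 115 (94.9 to 138.0). Neither figure concerns a comparison of arms.

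**Inputs for the check.**

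- Total of 115 patients (Sample size).
- Allocation 1:1: assumed. The randomization section says only that the system "will employ variable block sizes, stratified by ICU site".
- Even split between normal and abnormal day-7 PCT: assumed, and varied below.
- Mortality equal in both arms, 15 to 35%: assumed; the article gives no rate.
- Margin of 10 points and one-sided alpha of 0.025: assumed; the article gives neither.

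**Subgroup size.** 115 / 4 = 28.75, about 29 per arm per subgroup; 115 / 2 = 57.5 per arm in the whole pilot.

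**Precision.** Half-width = 1.96 × √(2p(1−p)/n). This needs no margin.

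| Mortality p | Subgroup (n = 28.75 per arm) | Whole pilot (n = 57.5 per arm) |
|---|---|---|
| 15% | 18.5 points | 13.1 points |
| 25% | 22.4 points | 15.8 points |
| 35% | 24.7 points | 17.4 points |

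**Power with truly equal arms.** Power = Φ(margin/SE − 1.96). At p = 0.25, SE = √(0.375/28.75) = 0.114. For a 10-point margin this gives Φ(0.876 − 1.96) = Φ(−1.084) = 0.139, about 14% per subgroup. For the whole pilot, SE = 0.081 and the power is about 24%.

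**What 80% power would need at 25% mortality.** With 28.75 per arm, a margin of (1.96 + 0.84) × 0.114 = 0.32, or 32 points. With a 10-point margin, 295 patients per arm per subgroup.

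**Sensitivity.**

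- *PCT split.* If a subgroup holds 20 to 80% of patients (11.5 to 46 per arm), the power for a 10-point margin at 20 to 30% mortality runs from 8 to 22%. What one subgroup gains the other loses, and deaths or missed samples before day 7 reduce both.
- *Mortality.* With an even split and 10 to 40% mortality, the power for a 10-point margin is 24% down to 12%.
- *Total size.* With 139 patients instead of 115 there would be 139/4 = 34.75 per arm per subgroup. At 25% mortality the half-width is 1.96 × √(0.375/34.75) = 20.4 points, and the power is Φ(0.963 − 1.96), about 16%. Whether 115 is the right number for adherence does not change the result.

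**The case against.** Four points can be made for the plan.

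- **No outcome is named, so there is no outright contradiction.** This stands in part. The PCT section speaks of clinical outcomes in general, and the sections on secondary outcomes and the DSMC concern mortality. The conflict is inferred from how the article uses non-inferiority elsewhere (survival in Background, mortality in Analysis of secondary outcomes). It is the natural reading, but it is conditional.
- **The wording is to confirm whether, not to confirm that.** This is true, and the rationale for fixed durations gives PCT a softer aim, incremental prognostic value. But the sentence still promises an answer, and the sample cannot supply one in either direction.
- **The study may mean the main trial.** Trial status allows the pilot to become internal, and the PCT assays wait until the end of the study. On that reading 29 per arm per subgroup would not apply. However, the roll-over is conditional, and Frequency of analyses places the analyses at completion of the pilot. If the main trial was meant, the sentence should say so.
- **The margin may be given elsewhere.** Agreed. This is a condensed article, and a margin may stand in the full protocol or analysis plan, so its absence is no finding. The interval widths make the point without one.

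A reader might also infer that the sub-study could sway the decision to launch the main trial or lead to a PCT stopping rule. The document does not support either. Feasibility rests on recruitment and adherence alone, PCT results are withheld from the treating team, and the authors choose fixed durations over biomarker-guided ones.

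**Conclusion.** The point holds in a limited form. The PCT section commits the pilot to a non-inferiority answer in two subgroups that its size cannot deliver. If the outcome is survival or mortality, this is inconsistent with the sections on secondary outcomes, subgroup analyses and the DSMC. With 1:1 allocation, an even PCT split and 15 to 35% mortality, all assumed, each subgroup has about 29 patients per arm and a 95% half-width of 18.5 to 24.7 points. At 25% mortality and an assumed 10-point margin, the power with equal arms is about 14%. The other assumptions tried lead to the same conclusion.

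The primary feasibility outcomes, the sample size and the decision on the main trial are untouched. What is at stake is how one sub-study result may be worded and read.

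**What to change.** Replace the sentence in Blood samples for procalcitonin with:

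> In the pilot, risk differences by day-7 PCT subgroup will be reported with 95% CIs as exploratory, and no non-inferiority conclusion will be drawn; any non-inferiority test is left to the main trial.

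The outcome to which the risk differences refer should be named in the same place. This brings the section into line with the rest of the article. It needs no extra patients, samples or assays, and it does not commit the main trial to PCT sampling, which the article does not describe. The cost is that the pilot gives up a claim it could not have supported.
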